**Figure 1 fig1:**
[figure not shown]
Delta-wave degrees. Schematic sinusoidal wave illustrating the phase-based triggering of CLAS. In-phase stimulation is delivered during the up-slope (270–90°), whereas trough stimulation is delivered during the down-slope (90–270°). These directional, phase-specific effects allow CLAS to either enhance (*in-phase*) or disrupt (*anti-phase*) δ-wave expression.

*Anti-phase*: δ-wave troughs are detected when the following conditions are met: (1) the signal goes above 40 μV; (2) the signal then crosses 0 μV; (3) the difference in amplitude between the maximum (peak) and the current oscillatory activity is greater than 75 μV; and (4) the trough occurs between 500 and 2,000 ms after the detected peak. The auditory stimulation is triggered during the down-slope of the wave, between 90 and 270° (Figure 1). To avoid multiple detection within the same slow oscillation, the detection is paused until the filtered signal passes through 0 μV.

#### Auditory stimuli

2.1.5

The auditory stimuli are composed of binaural bursts of pink noise, also known as 1/f noise. The auditory stimuli last for 50 ms, with a 5 ms rising and falling slope respectively, and are delivered through a trigger box connected to the CLAS detection algorithm. Sound volume will be set at a maximum of 65 dB SPL at the ear canal (Henin et al., 2019).

#### Pre-anesthesia procedure

2.1.6

In the operating room (OR), the BIS index (Connor, 2022; Rampil, 1998), which monitors intraoperative hypnotic depth using 4 prefrontal electrodes, will be connected to the patient and anesthesia monitor. A 128-channel high-density EEG saline net (MagstimEGI) referenced to Cz will then be placed on the patient’s head (Figure 2). Hd-EEG impedances will be verified and maintained <50 kΩ for the study’s duration. The patient will be positioned supine, and all routine monitors will be installed, as per standard of care. The PMD200™ monitor, which assesses intraoperative pain levels through the NOL index using a finger sensor (Ben-Israel et al., 2013; Edry et al., 2016), will also be installed.

**Figure 2 fig2:**
[figure not shown]
Simplified closed-loop auditory stimulation (CLAS) setup. A high-density EEG cap (128 channels) records neural activity, while a single frontal channel (Fz) is used online by the CLAS algorithm for real-time δ-wave detection and stimulation triggering. The Bispectral Index (BIS^®^) provides continuous monitoring of hypnotic depth, and the Nociception Level (NOL^®^) index monitors nociceptive balance. The full EEG is simultaneously recorded in NetStation (MagstimEGI, v5.4.3. R) for offline analyses, while the CLAS software delivers auditory stimuli phase-locked to δ-wave peaks or troughs.

### General protocol

2.2

#### Anesthesia induction

2.2.1

The hd-EEG net will be connected to the amplifier. GA will be induced with propofol and remifentanil in target-controlled infusion (TCI) mode. Propofol target concentration at effect-site (Ce) will be set at 4 μg.mL^−1^ using the Schnider (Rampil, 1998) or Marsh (Marsh et al., 1991) model and adjusted to keep a BIS index value between 40 and 60. Remifentanil Ce will be set at 3 ng.mL^−1^ using the Minto model (Minto et al., 1997) to achieve a NOL index <10. To mitigate potential electromyographical interference with BIS and hd-EEG, rocuronium will be administered as a bolus dose of 0.8 mg.kg^−1^ once the patient no longer responds (Figure 3). Subsequently, endotracheal intubation will be performed, followed by initiation of mechanical ventilation. Remifentanil administration will be immediately halted after intubation upon cessation of painful stimuli. Impedance levels will be reassessed and adjusted to ensure they remain below 50 kΩ.

**Figure 3 fig3:**
[figure not shown]
*Timeline of the study protocol*. Following baseline EEG recording in the awake state (5 min), general anesthesia is induced with propofol and remifentanil. Objective 1 includes three stimulation conditions (*in-phase, anti-phase, sham*; 3 min each, with 20 s pauses). Objective 2 involves *in-phase* stimulation with standardized nociceptive input (*Pre-Pain, Pain*, *Post-Pain* epochs). Anesthetic doses, BIS (target 40–60), and NOL (target <10) are maintained stable throughout.

#### Procedures for SA1 and SA2 (part 1)

2.2.2

Once anesthesia dosage is stable, BIS values are 40–60, predicted remifentanil Ce is <0.5 ng.mL-1 and the NOL is below 10, in-ear earphones (ER2XR Earphones; Etymotic Research, IL, United States) will be placed in patients’ ears, through which the CLAS auditory stimulation will be provided binaurally. These earphones already provide a 32–45 dB attenuation. To further attenuate ambient sounds in the OR, noise-blocking earmuffs (Peltor Optime 105; 3 M, MN, United States), effective up to 105 dB of ambient noise, will be placed over the earphones. The hd-EEG-CLAS software package will then deliver *in-phase*, *anti-phase*, and Rest (*sham*) stimulation blocks for 3 min each, with 20-s pauses between each stimulation type (10 min total). This interval is considered sufficient to prevent any carryover effects, as CLAS has shown only stimulus-locked effects, and do not persist beyond the targeted slow oscillatory cycles (Ngo et al., 2013; Ngo et al., 2015). Given that anesthetic doses will be stable and no CLAS carryover effect is expected beyond each stimulated wave, no randomization of stimulation blocks will be conducted. Under general anesthesia, cortical dynamics may gradually deepen over time despite stable TCI and by applying *in-phase* stimulation first, we adopt a conservative design that minimizes the risk of falsely attributing time-dependent anesthetic deepening to stimulation effects. Minimal physical contact will be made with the participant, and a minimal noise level will be maintained in the OR throughout the study for optimal isolation of the CLAS effects.

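### The start conditions are checked before the earphones and earmuffs are fitted, so any transient response to the fitting would fall mainly on the in-phase block

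*Protocol article*

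**What the plan says.** Section 2.2.2 (Procedures for SA1 and SA2, part 1) fixes a sequence.

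1. The start conditions are met: "Once anesthesia dosage is stable, BIS values are 40–60, predicted remifentanil Ce is <0.5 ng.mL-1 and the NOL is below 10".
2. The same sentence then turns to the earphones: "and the NOL is below 10, in-ear earphones (ER2XR Earphones; Etymotic Research, IL, United States) will be placed in". They go into both ears and are said to attenuate sound by 32–45 dB.
3. Earmuffs, "effective up to 105 dB of ambient noise, will be placed over the earphones".
4. Stimulation starts: "The hd-EEG-CLAS software package will then deliver *in-phase*, *anti-phase*, and Rest (*sham*) stimulation blocks for 3 min each". A pause of 20 s separates the blocks, and the article puts the whole of Part 1 at 10 min.

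The order is the same for everyone: "no randomization of stimulation blocks will be conducted". Two reasons are given: CLAS effects do not carry over, and putting in-phase first is conservative against gradual deepening of anesthesia. The section also says "Minimal physical contact will be made with the participant", with the aim of isolating the CLAS effects.

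Section 2.2.1 stops remifentanil after intubation, so a wait for its predicted concentration to fall is already part of the procedure.

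**The concern.** As written, the check on the patient's state comes one step too early. It describes the patient before both ears are handled and before the acoustic surroundings change. Every block runs afterwards, with the ears plugged and covered. For an auditory intervention, that is not the state in which the conditions were confirmed.

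The article treats contact and arousal as relevant. It asks for minimal contact, and sections 1.4 and 1.8 say that nociceptive input can act on arousal systems and disrupt slow waves. If fitting the devices provoked a short-lived response, in-phase would receive most of it, because in-phase always comes next. Sham starts 400 s after in-phase starts. With one order in all 30 patients, the within-subject comparison cannot separate such a response from the in-phase effect. Neither reason given for the fixed order covers it, since both concern other time effects.

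There is also a possible knock-on effect. Section 2.1.4 triggers in-phase sounds only when the signal passes set voltage thresholds, so a temporary fall in delta amplitude could reduce the number of stimuli delivered in that block.

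**Working it through.** **Timeline (section 2.2.2).** Three blocks and two pauses: 3 × 180 + 2 × 20 = 580 s, or 9 min 40 s. With a third pause before Part 2: 3 × 180 + 3 × 20 = 600 s. The stated 10 min is reproduced. In the listed order, and counting from the start of block 1, in-phase runs 0–180 s, anti-phase 200–380 s and sham 400–580 s.

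**Share of a fitting response in each block.** Assumptions, none from the documents: the response has initial size D when block 1 starts and decays exponentially with time constant τ. The mean over a block from a to b seconds is D × (τ/180) × [exp(−a/τ) − exp(−b/τ)]. For in-phase at τ = 60 s this is (60/180) × (1 − exp(−3)) = 0.317.

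| τ | In-phase | Anti-phase | Sham | In-phase − sham | In-phase share of the three-block sum |
|---|---|---|---|---|---|
| 30 s | 0.166 | 0.000 | 0.000 | 0.166 | 99.9% |
| 60 s | 0.317 | 0.011 | 0.000 | 0.316 | 96% |
| 120 s | 0.518 | 0.098 | 0.018 | 0.499 | 82% |

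For scale only, an initial BIS rise of 5 points would add 5 × 0.166 = 0.8 to 5 × 0.518 = 2.6 points to the in-phase mean.

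**Effect on a paired comparison.** n = 30 is from section 2.1.2, which gives no effect size, SD or power. I use a two-sided paired t-test at 5%, noncentral t with 29 df and noncentrality d√30. Power of 80% then needs a standardized paired difference of about 0.53. If a bias opposes a true difference of 0.53:

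- bias 0.1: power 62%
- bias 0.2: power 42%
- bias 0.3: power 23%

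With no true effect, a bias of 0.2 raises the two-sided rejection rate from 5% to 18.5%. Nearly all of this (18.4 points) lies in the direction of the bias; the other tail falls from 2.5% to 0.13%.

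**Linking the two steps.** The 0.2 is not derived from the decay model. To produce it, D would have to be 0.2/0.166 = 1.2, 0.2/0.316 = 0.63 or 0.2/0.499 = 0.40 SD of the paired difference, for τ = 30, 60 or 120 s. The documents give nothing to judge whether that is likely.

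**Direction.** An arousal would lower delta activity and raise BIS during in-phase. Sections 1.8 and 4.2 predict the opposite for in-phase: higher amplitude and slightly lower BIS. The bias would therefore hide the predicted effects.

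**What a contact-free interval does.** With 60 s between fitting and block 1, the in-phase minus sham remainder falls to 0.12 (τ = 60 s) or 0.30 (τ = 120 s). With 180 s it falls to 0.02 or 0.11.

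**The case against.** The strongest reply is that the response is hypothetical. Nothing in the article says that placing earphones in an intubated, paralysed patient at BIS 40–60 changes EEG, BIS or NOL. That stands: D, τ and the 0.2 SD are all assumptions.

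Several stronger readings are tempting, but the documents do not support them.

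- *That there is no settling time or re-check.* The article does not mention one, but it condenses a fuller protocol. The wording that introduces the blocks gives order, not immediacy; section 2.2.3, by contrast, says expressly that Part 2 follows at once. The Figure 3 caption also says that doses, BIS and NOL are kept stable throughout. What remains is the written order, which puts the check before the fitting.
- *That only in-phase follows the handling.* All three blocks do; in-phase is the nearest. At τ = 120 s, anti-phase still keeps about 10% of the shift.
- *That electrode impedances go unchecked once the earmuffs are on.* Section 2.2.1 says "Impedance levels will be reassessed and adjusted to ensure they remain below" 50 kΩ before the earmuffs are fitted, but section 2.1.6 commits to that limit for the whole study.
- *That the trial would falsely show enhancement.* An arousal works against that hypothesis, as the 0.13% tail shows.

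It can also be said that this is one instance of the fixed block order. In part it is: a balanced order would spread the response across conditions. It would still leave extra variation in whichever block came first, whereas moving the fitting step reduces the response at its source, even if the order stays fixed.

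**Conclusion.** The point holds as a minor one about sequence. The start conditions are read before the last planned head contact and in a different acoustic state from the blocks they are meant to qualify. Any transient response to fitting would be confounded mainly with in-phase.

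The likelier cost, if the response is an arousal, is a missed enhancement. A secondary risk concerns SA2, whose hypothesis speaks only of altered anesthetic depth: a BIS rise in the in-phase block could be taken for a stimulation effect, although section 4.2 expects a slight fall. In anti-phase, the remainder relative to sham at τ = 120 s is 0.098 − 0.018, or about 8% of the initial shift. That small part would favour the predicted disruption.

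The sizes depend on the assumed decay and bias. The sequence itself is stated in the article.

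**What to change.** Reorder section 2.2.2. Fit the earphones and earmuffs after intubation, during the wait for remifentanil washout that the procedure already contains. Then apply the start conditions exactly as already stated, with both devices in place and after a short contact-free interval of fixed length, and begin block 1. No dose, target or clinical rule changes.

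The cost is one reordered paragraph and earphones worn a few minutes longer. The interval removes a brief response but only part of a slow one, so its length should be written down and kept the same for every patient.

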### Objectives and hypothesis

1.8

The primary objective of this study is to determine whether CLAS can modulate *δ*-waves (0.1–4 Hz) during propofol-induced GA. Our central hypothesis is that CLAS can effectively enhance δ-waves during surgical anesthesia, and that this modulation will co-occur with changes in EEG/network features commonly observed in more stable anesthetized dynamics, while remaining inferential with respect to consciousness. While propofol enforces *δ*-waves dynamics via GABA-A potentiation (Brown et al., 2011; Franks, 2008), nociceptive input can still engage ascending pathways and modulate cortical state, challenging the maintenance of hypnosis (Brown et al., 2010; Garcia-Larrea and Bastuji, 2018). Consequently, our secondary objective is to assess whether the modulatory effects of *in-phase* CLAS on *δ*-waves during general propofol anesthesia are preserved in the presence of nociceptive inputs. Because nociception has been shown to interact with cortical arousal systems and transiently disrupt slow-wave dynamics (Bonhomme et al., 2016; Garcia-Larrea and Bastuji, 2018; Plourde et al., 2006), demonstrating that CLAS maintains or augments SWA under these conditions would provide critical translational evidence for its potential intraoperative application.

We will test these objectives through the following specific aims:

*Specific Aim 1 (SA1): Characterize the effect of in-phase and anti-phase CLAS on δ-wave morphology and topography, relative to sham stimulation*. We hypothesize that *in-phase* CLAS will increase amplitude, slope, duration, and density of δ-waves, decrease frequency and transition frequency, and will increase SWA power compared to *sham*. This effect will be most pronounced over frontal derivations, and will propagate posteriorly. We hypothesize that *anti-phase* CLAS will disrupt the intrinsic timing and propagation of δ-waves compared with *sham*, resulting in reduced amplitude, flatter slopes, lower transition frequency and decreased SWA power.

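### One fixed block order confounds stimulation with elapsed time, and the protocol's 'conservative' argument reverses for anti-phase versus sham

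*Protocol article*

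**What the plan says.** Section 2.2.2 (Procedures for SA1 and SA2) runs "stimulation blocks for 3 min each, with 20-s pauses between each stimulation type (10 min total"). It rules out randomisation because doses are stable and "no CLAS carryover effect is expected beyond each stimulated wave, no randomization of stimulation blocks will be conducted". It then accepts that "cortical dynamics may gradually deepen over time despite stable TCI" and argues that, with in-phase applied first, "we adopt a conservative design that minimizes the risk of falsely attributing time-dependent anesthetic deepening to stimulation effects".

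Only the first position is stated outright. That anti-phase precedes sham is read from the order of listing, which is the same in section 2.2.2 and in the Figure 3 caption: "Objective 1 includes three stimulation conditions (*in-phase, anti-phase, sham*; 3 min each, with 20 s pauses"). The figure itself is not shown.

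Section 1.8 (SA1) predicts that anti-phase, compared with sham, will disrupt delta-waves, "resulting in reduced amplitude, flatter slopes, lower transition frequency and decreased SWA power". Section 4.1 (H1) repeats the prediction for amplitude, slope and power. Section 4.2 (H2) adds that anti-phase may raise BIS.

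Sections 3.7.1 and 3.7.2 compare the three blocks by repeated-measures ANOVA and t-tests. Age and sex are the only covariates named for the delta-wave metrics, and neither section names a time or period term. The limitations in section 6 do not mention block order.

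**The concern.** With one order for everyone, each condition occupies one time slot. A planned Part 1 comparison of two conditions is therefore also a comparison of two times. Absence of carryover does not answer this: carryover is an effect of one block persisting into the next, while drift is a change that would occur with no stimulation at all. A 20-second pause does nothing about drift, and neither does the within-subject design.

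The defence offered addresses one direction only. It works where the earlier block is expected to show more delta activity than the later one, as for in-phase versus sham. SA1 and H1 have a second half, in which the earlier block (anti-phase) is expected to show less than the later one (sham). There the drift that the protocol anticipates pushes the data towards the hypothesis. At stake is the claim of phase-specific modulation, which needs both halves.

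**Working it through.** **Inputs from the protocol.** Three blocks of 180 s with 20-s pauses (section 2.2.2); order in-phase, anti-phase, sham (sections 2.2.2 and Figure 3 caption); 30 patients, within-subject (section 2.1.2). Duration check: 3 × 180 + 2 × 20 = 580 s (9 min 40 s) with two pauses, or 600 s with three, consistent with the stated 10 min. The sample size of 30 comes without effect size, SD, alpha or power, so it cannot be reproduced.

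**Block midpoints.** 90, 290 and 490 s, i.e. 1.50, 4.83 and 8.17 min.

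**Sign of the bias.** Let delta activity rise linearly by g per minute.
- In-phase minus sham = true effect + (1.50 − 8.17)g = true effect − 6.67g. The prediction is positive, so the bias works against it.
- Anti-phase minus sham = true effect + (4.83 − 8.17)g = true effect − 3.33g. The prediction is negative, so the bias works towards it.
- BIS: deepening lowers BIS in the later sham block, so anti-phase looks higher, as H2 predicts.
- Transition frequency: SA1 predicts it lower under anti-phase. Deepening would presumably lower it in the later sham block, so this item is not favoured by drift.

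**Size under assumed drift.** Assumptions, none given in the protocol: g in SD of the paired difference per minute, linear drift, paired t-test, two-sided 5%, n = 30 (29 df). With no true effect, the standardised difference is −3.33g and the rejection rate follows from the noncentral t with noncentrality −3.33g × √30.

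| g (SD/min) | Standardised bias, anti-phase vs sham | False-positive rate |
|---|---|---|
| 0 | 0 | 5% |
| 0.05 | −0.17 | 14% |
| 0.10 | −0.33 | 42% |
| 0.15 | −0.50 | 75% |

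**Cost on the in-phase side.** A true standardised in-phase effect of 0.53 has 80% power without drift. The bias cancels it entirely at g = 0.53 / 6.67 ≈ 0.08 per minute.

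**Check of the remedy.** All six orders with 5 patients each were simulated (40,000 replicates, no true effect) at drifts of 0, 0.1, 0.2, 0.3 and 0.5 SD per block step. One step is 3.33 min, so 0.5 per step equals 0.15 per minute. Each condition then has the same mean position. The mean anti-phase minus sham bias was within 0.001 SD of zero throughout, and the type I error of the unadjusted paired t-test was 5.0%, 4.7%, 4.1%, 3.4% and 1.7%. A period term would remove that conservatism.

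**The case against.** The strongest reply is that the central hypothesis is enhancement by in-phase stimulation and that SA2 concerns in-phase only. For those contrasts the anticipated deepening does work against the hypothesis, as the protocol says, and the price is power rather than false positives. This stands, and it confines the anti-conservative exposure mainly to anti-phase versus sham.

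Other limits also stand. Anti-phase before sham is inferred from two consistent listings; if sham came second, the reversal would not apply. Every drift size above is assumed, and the 75% figure needs a shift of 1 SD between the in-phase and sham midpoints (6.67 × 0.15) under stable dosing.

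Three stronger readings are tempting but not supported.
- *That no analysis could separate condition from time.* Part 2 (section 2.2.3) opens with a minute of in-phase stimulation before any nociceptive input, with its midpoint at about 10.2 to 10.5 min. In-phase is thus observed before and after the other two blocks, and drift could be estimated from it if drift is linear and there is no carryover. This is weak (1 min against 3 min) and unplanned, since section 3.7.3 uses that epoch only for SA3, but it rules out the categorical claim.
- *That the no-carryover premise contradicts SA2 and SA3.* Those aims predict differences while stimulation is running, and the post-pain period lies inside one continuous in-phase block. Neither implies persistence across a pause.
- *That the state will lighten and so favour in-phase.* Section 2.2.1 says "Remifentanil administration will be immediately halted after intubation upon cessation of painful stimuli", and blocks may start once its predicted effect-site concentration is below 0.5 ng/mL, so some further decline is possible. But deepening is the only direction that the protocol anticipates; lightening is a possibility, not an expectation.

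**Conclusion.** The concern holds for the Part 1 comparisons as planned. Condition is confounded with elapsed time, no time term is named, and the stated justification covers in-phase versus sham but not anti-phase versus sham. In the latter, the drift that the protocol itself anticipates would mimic the predicted result for amplitude, slope, SWA power and BIS, though not for transition frequency.

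The sign of the bias follows from the documents, given that sham is last. The size does not: false-positive rates of about 14% to 75% correspond to assumed linear drifts of 0.05 to 0.15 SD of the paired difference per minute. A reader should not conclude that every SA1 and SA2 contrast is biased towards its hypothesis, or that the data would be beyond any adjustment. What can be said is that a significant anti-phase result could not be told from drift by the planned analysis, and that a null in-phase result could reflect a true effect offset by drift.

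**What to change.** Randomise or counterbalance the block order over the six possible sequences, 5 patients each (6 × 5 = 30), and include period as a fixed effect in the Part 1 models. Delete the 'conservative design' statement or limit it to in-phase versus sham.

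If enrolment has started, counterbalance the remaining patients, report the fixed-order patients separately, treat their anti-phase versus sham contrast as exploratory, and state the confounding as a limitation.

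The cost is a sequence list and a short amendment, with no added patients, time or procedures. There are two small downsides. Period uses two degrees of freedom. Part 2 would also follow different final blocks: a third of patients would enter it after each condition. That is harmless on the protocol's own no-carryover premise and can be handled by recording the sequence and including it in the SA3 model.
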